**Secondary outcomes — nutritional status.** Secondary nutritional outcomes include the skeletal muscle index measured at the third lumbar vertebral level on abdominopelvic computed tomography; composite nutritional and inflammatory–nutritional indices comprising the Nutritional Risk Screening 2002 (NRS-2002), GLIM criteria, Prognostic Nutritional Index (PNI), C-reactive protein–to-albumin ratio (CAR), and modified Glasgow Prognostic Score (mGPS); serum nutritional biomarkers (albumin, prealbumin, total protein); and longitudinal changes in body weight, body composition assessed by multifrequency segmental bioelectrical impedance analysis (InBody 770; InBody Co., Ltd., Seoul, Republic of Korea), and handgrip strength assessed by hand dynamometry.

**Secondary outcomes — glycemic control.** Postoperative glycemic outcomes comprise the proportion of participants with any blood glucose ≥180 mg/dL during POD 0 through POD 5, stratified by baseline diabetes status, together with the cumulative insulin requirement during the same period. Because the investigational formulation also delivers less carbohydrate, these glycemic outcomes partly reflect the compositional difference in carbohydrate load and are interpreted accordingly.

**Secondary outcomes — postoperative complications.** Postoperative complications occurring within 30 days after surgery are classified using the Clavien–Dindo classification. Specific complications captured include surgical site infection; pneumonia; delayed gastric emptying; and anastomotic leak.

**Secondary outcomes — functional recovery.** Functional recovery milestones aligned with the institutional ERAS pathway include time to first defecation, time to tolerate ≥50% of a soft diet for 24 hours, time to independent corridor ambulation, and length of postoperative hospital stay. Patient-reported recovery outcomes are assessed at POD 14, 1 month, 3 months, 6 months, and 12 months, and encompass oral intake (proportion relative to preoperative volume and meal frequency), early satiety, appetite loss, gastrointestinal symptoms (nausea, vomiting, dumping, reflux, diarrhoea, constipation), oral nutritional supplement use, and habitual physical activity. Clinical events—including emergency department visits, readmissions, and interventions—are captured through 12 months.

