**Secondary outcomes — Nutritional status**			
Nitrogen balance trajectory	Same formula as the primary outcome, applied at the early postoperative time point	POD 3	Two-sample t-test or Wilcoxon rank-sum
Sarcopenia index	Skeletal muscle index measured at the third lumbar vertebral level on abdominopelvic computed tomography (cm²/m²)	Baseline, 3, 6, 12 months	Paired t-test (within-group); two-sample t-test (between-group); Chi-square or Fisher’s exact (sarcopenia incidence)
Nutritional risk and inflammatory–nutritional indices	Nutritional Risk Screening 2002 (NRS-2002), Global Leadership Initiative on Malnutrition (GLIM) criteria, Prognostic Nutritional Index (PNI), C-reactive protein–to-albumin ratio (CAR), modified Glasgow Prognostic Score (mGPS)	POD −1, POD 5, 1, 3, 6, 12 months	Two-sample t-test or Wilcoxon rank-sum (continuous); Chi-square or Fisher’s exact (categorical)
Serum nutritional biomarkers	Albumin, prealbumin, total protein	POD −1, POD 5; albumin/total protein additionally at 1, 3, 6, 12 months	Paired t-test (within-group); two-sample t-test (between-group)
Body weight, body composition, handgrip strength	Body weight; multifrequency segmental bioelectrical impedance analysis (InBody 770; InBody Co., Ltd., Seoul, Republic of Korea); handgrip dynamometry (kg)	Body weight: POD −1 and 14 days, 1, 3, 6, 12 months; InBody and handgrip: POD −1, 1, 6, 12 months	Linear mixed-effects model for repeated measures (random intercept per participant; fixed effects for treatment, time, and treatment × time interaction); between-group differences reported with 95% confidence intervals

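### Table 4 names no baseline-adjusted between-arm comparison for skeletal muscle index, and does not identify the contrast in the mixed model for weight, body composition and grip

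*Protocol article*

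**What the plan says.** All the relevant text is in the nutritional-status block of Table 4 in the protocol article. The sentence introducing that table, at the end of the Outcomes section, presents it as the place where the planned analysis of each outcome is set out.

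- **Skeletal muscle index** is measured at "Baseline, 3, 6, 12 months". The analysis entry gives a paired t-test within each arm and then "two-sample t-test (between-group); Chi-square or Fisher", where the categorical test is for sarcopenia incidence. Baseline is certain to enter only the paired tests, which are made within each arm.
- **Weight, body composition and grip** have the pre-treatment visit in the same list as the follow-up visits: "Body weight: POD −1 and 14 days, 1, 3, 6, 12 months" and "InBody and handgrip: POD −1, 1, 6, 12 months". The model is a linear mixed model with "random intercept per participant; fixed effects for treatment, time, and treatment × time interaction". Table 4 asks for between-group differences with 95% confidence intervals, but does not say which model term or combination of terms supplies them.
- **The stated target** in the Outcomes section is "longitudinal changes in body weight, body composition assessed by multifrequency segmental bioelectrical impedance analysis" and handgrip strength. Skeletal muscle index is listed there separately, as a measured value.

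The footnote to Table 4 makes all of these exploratory. The only ANCOVA in the article is the adjusted analysis of POD 5 nitrogen balance, in the Statistical analysis section.

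**The concern.** Muscle area, weight and grip strength are strongly person-specific, so a participant's baseline value usually predicts much of the later one. An arm comparison that leaves baseline out carries the full between-person spread and any chance difference present before treatment. Within-arm paired tests do not repair this: one arm may change significantly and the other not without the arms differing.

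The mixed model raises a related question. With POD −1 as an outcome level and a free treatment effect, the model fits a separate arm difference at a visit where randomisation makes the expected difference zero. How well baseline is then used depends on which contrast is reported, and Table 4 does not say. Since these outcomes are to be read through estimates and confidence intervals, the width of those intervals is what is at stake.

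**Working it through.** **The plan's own figure.** The Sample size section assumes a 3 g/day difference, SD 5, two-sided 0.05 and 80% power. The normal formula gives 2 × (1.960 + 0.842)² × 25/9 = 43.6, so 44 per arm, and 44/0.8 = 55 per arm. Both figures reproduce. They concern nitrogen balance; the article gives no power or precision figure for the muscle outcomes. I use 55 per arm below as a best case, because the 20% allowance is said to cover the POD 5 outcome and not attrition over 12 months.

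**Variance under each reading.** Take equal SD at both visits and correlation ρ between baseline and follow-up. Relative to a comparison of follow-up values, the variance of the arm difference is:

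- follow-up value only: 1
- change from baseline: 2(1 − ρ)
- adjusted for baseline (ANCOVA): 1 − ρ²

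The ratio of adjusted to change-score variance is (1 − ρ²) / [2(1 − ρ)] = (1 + ρ)/2. The ratio of interval widths, follow-up-only to adjusted, is 1/√(1 − ρ²). The documents do not give ρ, so the range is an assumption.

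| ρ (assumed) | Change, 2(1 − ρ) | Adjusted, 1 − ρ² | Width, follow-up-only / adjusted | Variance, adjusted / change |
|---|---|---|---|---|
| 0.5 | 1.00 | 0.75 | 1.15 | 0.75 |
| 0.7 | 0.60 | 0.51 | 1.40 | 0.85 |
| 0.8 | 0.40 | 0.36 | 1.67 | 0.90 |
| 0.9 | 0.20 | 0.19 | 2.29 | 0.95 |

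**Detectable difference.** With 80% power at 55 per arm, it is √(2/55) × 2.802 × √(relative variance), in SD units.

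- Follow-up only: 0.191 × 2.802 = 0.534 at any ρ.
- Change: 0.534, 0.414, 0.338 and 0.239 for ρ = 0.5, 0.7, 0.8 and 0.9.
- Adjusted: 0.463, 0.382, 0.321 and 0.233.

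At 44 per arm the follow-up-only figure is 0.597.

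**Chance imbalance.** The standard error of a baseline arm difference at 55 per arm is √(2/55) = 0.19 SD. Given a baseline gap g, a follow-up comparison is shifted by ρg and a change comparison by −(1 − ρ)g. At ρ = 0.8 and g = 0.19 these are +0.15 SD and −0.04 SD. Baseline adjustment removes the shift.

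**What the mixed model estimates.** With complete data and POD −1 as the reference visit, three identities hold, confirmed to about 1e-15 in simulated trials:

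- the treatment coefficient is the raw baseline difference;
- the interaction at a visit is the raw change-score difference;
- treatment plus interaction is the raw difference at that visit.

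In 200 simulated trials (55 per arm, four visits, ρ = 0.8, no missing data), the SD of the last-visit estimate was 0.191 for treatment plus interaction, 0.122 for the interaction, 0.116 for the same model with a common baseline mean, and 0.116 for ANCOVA.

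**The case against.** A reader might infer from Table 4 that muscle index is compared on follow-up values and that the mixed model ignores baseline. The documents support neither.

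The table does not state the response for the muscle index t-test. The serum biomarker row has the same wording, and the footnote defines the prealbumin endpoint from that row as a change from POD −1. The same notation can therefore cover a change score. In the mixed model, the treatment-by-time contrast is itself a change-from-baseline comparison and fits the stated aim of longitudinal change. If that contrast is reported, little is lost: SD 0.122 against 0.116 at ρ = 0.8.

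It can also be said that ANCOVA gains least over change scores when ρ is high, which is the likely case for these measures; that the outcomes are exploratory and touch neither the primary analysis nor the sample size; and that SAP v1.0, not shown, may name response and contrast.

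Most of this stands, and it limits the size of the point. It does not remove it. Table 4 is offered as the statement of planned analyses and names specific methods, so the choice of method can be judged as printed. On either reading, baseline adjustment is at least as precise in expectation. At ρ = 0.5 a change score does no better than ignoring baseline, while adjustment still saves a quarter of the variance.

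**Conclusion.** The point holds as a free improvement, not as an error that invalidates a result. Table 4 names no baseline-adjusted arm comparison for skeletal muscle index and leaves value or change open. Its mixed model gives POD −1 an unconstrained arm difference and does not identify the contrast.

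The size depends on the reading. For ρ from 0.5 to 0.9, adjusted variance is 75% to 19% of that of a follow-up-only comparison, and 75% to 95% of that of a change-score comparison. Even in the worse case the unadjusted intervals are 1.15 to 2.3 times as wide, so it would overstate the matter to call them several times too wide over the whole range. Nor is there bias: under randomisation every one of these analyses is unbiased, and the cost is precision and carry-over of chance imbalance.

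The figures assume equal variances at both visits and complete data, and leave out the small cost of estimating the baseline slope. Attrition to 12 months is not given and would widen all intervals.

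**What to change.** Change the Table 4 entries and the matching SAP text:

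- **Skeletal muscle index:** compare arms by ANCOVA at 3, 6 and 12 months, or by one repeated-measures model over those visits, with baseline index as covariate.
- **Weight, body composition and grip:** either take POD −1 as a covariate and model only the later visits, or keep it as a response with a common arm mean at baseline.
- **Reporting:** name the contrast as the visit-specific adjusted difference between arms, with its 95% confidence interval.
- **Paired tests:** if kept, present them as descriptive and not as evidence of a treatment effect.

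The cost is wording. The baseline values are already scheduled, no further data are needed, and the primary analysis and sample size are unchanged.

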**Safety outcomes**			
Adverse events, adverse drug reactions, and serious adverse events	Any adverse event, adverse drug reaction (per investigator’s causality assessment), or serious adverse event recorded throughout the intervention and follow-up period	Through 12 months	Descriptive (number of participants, events, incidence proportion); Chi-square or Fisher’s exact test for between-group comparison
Laboratory safety	Aspartate and alanine aminotransferase, blood urea nitrogen, serum creatinine, glucose, electrolytes	POD −1, POD 3, POD 5, 1, 3, 6, 12 months	Descriptive summary; between-group comparison at each timepoint

All analyses will be performed on the intention-to-treat population, with per-protocol analysis as a sensitivity analysis. Two-sided α = 0.05 will be used throughout. The single primary endpoint is the sole confirmatory analysis. The two key secondary endpoints — POD 3 nitrogen balance (reported with the nitrogen balance trajectory) and the early change in serum prealbumin, defined as the change from the preoperative (POD −1) baseline to POD 5 — are controlled for family-wise error at 0.05 by the Holm procedure, independently of the primary result; all other secondary outcomes are exploratory and reported with 95% confidence intervals without multiplicity adjustment. For the primary endpoint, genuine missing data are handled by multiple imputation under the missing-at-random assumption as the primary approach, with complete-case analysis as a sensitivity analysis and a delta-adjusted (tipping-point) analysis under missing-not-at-random assumptions. Full specifications are given in the dated statistical analysis plan (SAP v1.0, 21 July 2026). Abbreviations: APCT, abdominopelvic computed tomography; CAR, C-reactive protein–to-albumin ratio; GLIM, Global Leadership Initiative on Malnutrition; mGPS, modified Glasgow Prognostic Score; NRS-2002, Nutritional Risk Screening 2002; ONS, oral nutritional supplement; PNI, Prognostic Nutritional Index; POD, postoperative day.

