### Sample size

The primary outcome is the nitrogen balance on POD 5, expressed in grams per day, compared between the two arms. The sample size calculation is based on a two-sample t-test of independent means. In the absence of a directly comparable randomized trial of high-protein versus conventional PN in patients undergoing gastric cancer surgery, the assumed effect size and variability were derived from related studies of postoperative nitrogen balance under modified protein and amino-acid support [13,14] and from clinical considerations of the smallest between-group difference that would be regarded as clinically meaningful in this population. A between-group mean difference of 3 g/day in postoperative nitrogen balance was assumed, with a common standard deviation of 5 g/day. Using a two-sided significance level of 0.05 and statistical power of 80%, the minimum required sample size is 44 participants per arm (88 participants in total). Anticipating a combined withdrawal, protocol non-completion, or missing primary outcome rate of approximately 20%, the planned enrollment is increased to 55 participants per arm, giving a total target enrollment of 110 participants. The 20% inflation is an allowance for missingness of the POD 5 primary outcome — incomplete 24-hour collection, early events, PN discontinuation, or death before POD 5 — rather than attrition during the 12-month follow-up; it is a conservative estimate consistent with the completeness typically achievable for a fixed-day metabolic endpoint and with attrition reported in comparable post-gastrectomy nutrition trials [26,27]. Because scheduled PN coverage on POD 5 is 50%, the between-arm difference in delivered nitrogen on the primary-endpoint day is approximately 1.0–1.2 g/day, with a cumulative difference of roughly 8 g over the six-day intervention; the assumed 3 g/day balance difference therefore exceeds the single-day intake difference and, if observed, would indicate a genuine difference in nitrogen retention rather than intake alone. The sensitivity of statistical power to the assumed effect size and standard deviation is summarized in S5 Table.

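### The random-intercept-only mixed model for weight, body composition and handgrip will misstate confidence intervals for change from baseline if within-participant correlation decays over the 12 months

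*Protocol article*

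**What the plan says.** Table 4 (secondary outcomes, nutritional status) puts body weight, bioimpedance body composition and handgrip under one analysis: "Linear mixed-effects model for repeated measures (random intercept per participant; fixed effects for treatment, time, and treatment × time interaction"), with "between-group differences reported with 95% confidence intervals". The visits are unequally spaced: "Body weight: POD −1 and 14 days, 1, 3, 6, 12 months; InBody and handgrip: POD −1, 1, 6, 12 months". That is six visits for weight and four for the other two.

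The Outcomes section describes what is of interest as "longitudinal changes in body weight, body composition assessed by multifrequency segmental bioelectrical impedance analysis", and handgrip stands in the same list. The notes to Table 4 class these outcomes as exploratory ("all other secondary outcomes are exploratory and reported with 95% confidence intervals without multiplicity adjustment") and add that "Full specifications are given in the dated statistical analysis plan (SAP v1.0, 21 July 2026"). That plan is not available here. The row mentions no residual correlation, visit-specific variance, random slope or robust standard error.

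**The concern.** A random intercept with variance s_b² and independent residuals with variance s_e² gives variance s_b² + s_e² at every visit and correlation s_b²/(s_b² + s_e²) for every pair of visits. The day before surgery is then as strongly correlated with 12 months as with day 14. Over a year after gastrectomy it is plausible, though the article has no data on it, that participants' paths diverge, so that a 12-month value follows baseline less closely than a day-14 value does.

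The model would then give every change from baseline the same standard error, a compromise between a small early one and a large late one. These outcomes are to be reported through their 95% intervals without multiplicity adjustment. An interval that is too narrow at 12 months could therefore suggest a lasting effect of a six-day intervention where there is none.

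**Working it through.** **The plan's own figure.** The article states no variance or correlation for these outcomes. Its only design calculation is for the primary endpoint (difference 3 g/day, SD 5 g/day). It reproduces: 2 × (1.960 + 0.842)² × 25/9 = 43.6, so 44 per arm, and 44/0.80 = 55. This check takes only the 55 per arm from it.

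**Method.** Let Σ be the true covariance over T visits, with visit 0 as baseline. With complete data, categorical visit and separate arm-by-visit means, the random-intercept fit settles in large samples at v = mean of the diagonal of Σ and c = mean of its off-diagonal entries. With n per arm:

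- change from baseline: fitted SE = √[(2/n) × 2(v − c)]; true SE at visit j = √[(2/n) × (Σ_jj + Σ_00 − 2Σ_0j)];
- difference at one visit: fitted SE = √[(2/n) × v]; true SE = √[(2/n) × Σ_jj];
- coverage = 2Φ(1.96 × fitted SE / true SE) − 1.

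All covariances below are assumptions.

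**Scenario A, weight in kg.** n = 55; baseline SD 9; visit noise SD 0.7 (variance 0.49); individual slope SD 1.2 per square-root month (variance 1.44).

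- The sample variance of √month over the six visits is 1.594, so v − c = 0.49 + 1.44 × 1.594 = 2.786.
- Fitted SE of change, the same at every visit: √(2/55 × 2 × 2.786) = 0.45.
- True SE at 14 days (0.46 month): √[2/55 × (1.44 × 0.46 + 0.98)] = 0.24. The ratio is 1.84 and coverage about 100%.
- True SE at 12 months: √[2/55 × (1.44 × 12 + 0.98)] = 0.81. The ratio is 0.55 and coverage 72%.
- Difference at one visit: fitted SE 1.78 against a true 1.73 at 14 days and 1.90 at 12 months. Coverage is 95.6% and 93.4%.

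A simulation of 150 trials under these assumptions gave coverage for change of 100% at 14 days and 74% at 12 months.

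**Scenario B, weight, constant variance, correlation decaying exponentially to 0.9, 0.8 or 0.6 at 12 months.** For 0.8, the mean correlation is 0.910. At 14 days (taken as half a month) the correlation with baseline is 0.991 and the SE ratio is √[(1 − 0.910)/(1 − 0.991)] = 3.13, using unrounded values. At 12 months it is √(0.0904/0.20) = 0.67.

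**Scenario C, weight, random intercept plus linear slope.** Baseline between-participant variance 1, noise variance 0.02, SD of the 12-month slope component 0.25 or 0.5 of the between-participant SD. For 0.5, v − c = 0.0568 and the true variance of change at 12 months is 0.25 + 0.04 = 0.29. The ratio is √(2 × 0.0568/0.29) = 0.63.

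| Weight: true covariance | Change, 14 days | Change, 12 months | Single visit, 12 months |
|---|---|---|---|
| A | ≈100% | 72% | 93.4% |
| B, correlation to 0.9 / 0.8 / 0.6 | ≈100% | 81% / 81% / 82% | 95.0% |
| C, slope 0.25 / 0.5 | 98.2% / 99.9% | 86.1% / 78.0% | 94.5% / 92.9% |
| Equal correlation | 95.0% | 95.0% | 95.0% |

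**Body composition and handgrip (four visits, no day-14 visit).** Under B and C, coverage for change is 98.8–100% at 1 month and 83–89% at 12 months. Single-visit coverage at 12 months is 93–95%.

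**The case against.** Three objections carry weight.

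First, the error is conditional. The article gives no covariance data, and under equal correlation coverage is 95% throughout. That stands, and the figures above are illustrations only.

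Second, Table 4 promises between-group differences and does not say whether they are differences at a visit or in change from baseline. A reader might infer that the intervals at the early and late visits are simply wrong. The documents do not support that: with complete data and categorical visit, unequal correlation alone leaves a single-visit interval at 95%, and unequal variances moved it only to about 93–96%. The problem lies in the treatment-by-time contrasts. These still matter, because the Outcomes section speaks of longitudinal changes, the preoperative measurement is a listed timepoint and the interaction is in the model.

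Third, a random intercept is compatible with a residual correlation structure or robust standard errors, and the unseen analysis plan may add either. That is possible. But the article introduces Table 4 as giving the prespecified analyses, and the row names a random intercept as its only covariance term. The point challenges that stated choice, not the absence of detail.

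A reader might also infer that these outcomes carry no hypothesis tests. The notes to Table 4 say only that there is no multiplicity adjustment, and they set a two-sided α of 0.05 throughout.

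**Conclusion.** The point holds in a limited, conditional form. As written, the model imposes equal variances and equal correlations on unequally spaced visits over a year. If correlation decays or variance grows, intervals for between-arm differences in change from baseline are too wide early and too narrow late. Nominal 95% intervals for weight then cover about 98–100% at 14 days and 72–86% at 12 months; for body composition and handgrip they cover about 83–89% at 12 months.

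These figures assume independent residuals, categorical visit, complete data and the covariances listed. Dropout would make the results depend further on the covariance model. The consequence is small, because the outcomes are exploratory and neither the primary endpoint nor the two key secondary endpoints use this model.

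**What to change.** In Table 4 and the analysis plan, keep the fixed effects for treatment, visit and their interaction, state that visit is categorical, and replace the random intercept with an unstructured within-participant covariance. Use Kenward–Roger degrees of freedom and name heterogeneous Toeplitz as the fallback if the model does not converge. Say whether the reported contrast is the difference at each visit, the difference in change from baseline, or both. Adjusting for the baseline value as a covariate is optional.

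The cost is a line of wording in a dated amendment. No new data are needed, and the method is available in R, the stated software. The unstructured model has 6 × 7/2 = 21 covariance parameters for weight and 4 × 5/2 = 10 for the four-visit outcomes, against two now; 110 participants should support that, and the fallback covers failure. The expected study completion date is March 2028, so there is time to change this while the treatment labels are still coded.
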